### Statistical analysis

The sample size calculation is based on the aforementioned primary hypothesis (Table 2), that an enhanced diagnostic work-up consisting of cerebral and cardiac MRI (including contrast-enhanced angiography of the aortic arch and the carotid arteries) combined with a prolonged ECG-Monitoring (of up to 10 days duration) leads to a reduction in the number of strokes classified as cryptogenic from 30 to 25 % when compared to the routine diagnostic work-up at the Stroke Unit. A sample size of 396 patients which receive both the enhanced as well as the routine diagnostic work-up would provide a power of 79 % to detect a difference in the number of strokes classified as cryptogenic (from 30 % after routine diagnostic work-up to 25 % after enhanced diagnostic work-up, and with assumed 13 % discordant pairs: 9 % diagnosed as cryptogenic stroke by routine work-up but not according to enhanced diagnostic work-up, and 4 % diagnosed as cryptogenic stroke by enhanced work-up but not according to routine diagnostic work-up). The hypothesis will be tested using the McNemar-Test (two-sided, α = 0.05). An interim analysis (with a significance level of α1 = 0.004) will be performed when 264 patients (67 %) are enrolled in the study. If p is ≤ α1 at the interim analysis, the study will be terminated. When the study will be continued, the primary endpoint will be tested with α2 = 0.046 (two- tailed); the overall significance level will be 5 %.  Taking into account a drop-out rate of about 20 %, 475 patients will have to be enrolled in the study. 

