**Discussion:**

By comparing the results of routine diagnostic care to the study-specific MRI/ECG approach, the primary outcome of HEBRAS is the proportion of stroke patients with pathologic diagnostic findings. Predefined secondary outcomes are the association of stroke localization, autonomic dysbalance and cardiac dysfunction as well as the effect of impaired heart-rate-variability on long-term clinical outcome.

The investigator-initiated HEBRAS study will assess whether an enhanced MRI approach and a prolonged ECG monitoring yield a higher rate of pathological findings than current standard diagnostic care to determine stroke etiology. These findings might influence current diagnostic recommendations after acute ischemic stroke. Moreover, HEBRAS will determine the extent and clinical impact of stroke-induced cardiac damage.

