### Stroke etiology

Etiology will be determined according to TOAST [18] and ESUS criteria [4]. The following diagnostic findings will be regarded as pathologic and relevant to stroke etiology: atrial fibrillation of any type, sick sinus syndrome, bacterial or nonbacterial thrombotic endocarditis, ipsilateral carotid or intracranial stenosis of ≥ 50 % according to NASCET [19], left atrial or left ventricular thrombus, atrial myxoma, acute myocardial infarction resulting in wall motion abnormalities, akinetic left ventricular segment, dilated cardiomyopathy, systolic dysfunction with reduced left ventricular ejection fraction (<45 %), aortic plaque of ≥ 4 mm.

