### Study outcomes

The primary outcome of the HEBRAS study is the rate of pathologic findings relevant to stroke etiology in patients with acute ischemic stroke obtained by enhanced diagnostic MRI work-up combined with prolonged Holter-monitoring in comparison to findings obtained by the routine diagnostic work-up in this cohort of patients. The primary hypothesis is that the detection rate of pathologic findings can be increased by undergoing enhanced diagnostic MRI work-up combined with prolonged Holter-monitoring. The primary outcome and all secondary outcomes are listed in Table 2, and a flowchart of study specific data acquisition is provided in Table 3.

**Table 2 Tab2:** Primary outcome and secondary outcomes of the HEBRAS study

Primary outcome
• Detection rate of pathologic findings relevant to stroke etiology in patients with acute ischemic stroke obtained by enhanced diagnostic MRI work-up combined with prolonged Holter-monitoring in comparison to findings obtained by routine diagnostic work-up.
Secondary outcomes
• To assess the benefit of prolonged continuous ECG-monitoring in AIS patients to detect paroxysmal AF.
• To determine the proportion of patients with first detected paroxysmal AF by prolonged Holter-monitoring (for up to 5 days) after hospital discharge.
• To identify the impact of stroke localization on autonomic changes (as indicated by elevated urinary norepinephrine levels and measures of HRV) or cardiac dysfunction (as indicated by troponin T serum levels).
• To identify the impact of impaired HRV on recurrent vascular events and clinical outcome after AIS at 3 or 12 months after the index stroke, respectively.
• To assess the predictive value of imaging and biomarkers for AF-detection in patients with acute ischemic stroke.

**Table 3 Tab3:** Study flowchart of the HEBRAS study

	In-hospital stay				Follow-up	
	Admission	Day 1	Day ≥2	Discharge	3 months	12 months
Baseline data*	X					
Past medical history	X				X	X
Heart rate at rest (routine)	X	X	Daily	X		
Heart rhythm (routine)	X	X	Daily	X		
12-lead ECG	X					
24-hour Holter			(X)			
Additional ECG monitoring^a^	ongoing			ongoing^c^		
Respiratory rate	X	X	Daily			
Clinical signs of infection	X		X	X		
Leukocytes [per mm^3^]	X					
Creatinine [mg/dl]	X					
Potassium [mmol/l]	X					
Serum hs troponin I [ng/l]	X	X				
NT-proBNP [ng/l]		X				
Urine norepinephrine [nmol/l]		X				
Cardiac MRI		X				
MR angiography^b^		X				
Brain MRI		X				
NIHSS	X			X		

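### The power calculation uses cryptogenic classification, but the declared primary outcome is detection of listed pathologic findings, and the protocol never equates the two

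*Protocol article*

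**What the plan says.** **Declared outcome.** Study outcomes states: "The primary outcome of the HEBRAS study is the rate of pathologic findings relevant to stroke etiology in patients with acute ischemic stroke", enhanced against routine work-up. The hypothesis there reads: "The primary hypothesis is that the detection rate of pathologic findings can be increased". Table 2 has the same variable: "Detection rate of pathologic findings relevant to stroke etiology in patients with acute ischemic stroke obtained by enhanced diagnostic MRI work-up". The Discussion part of the Abstract has it per patient: "the primary outcome of HEBRAS is the proportion of stroke patients with pathologic diagnostic findings". The opening of the main Discussion again gives the aim as an increase in relevant findings.

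**Definition of a finding.** The Stroke etiology section introduces a list of cardiac, arterial and aortic abnormalities with "The following diagnostic findings will be regarded as pathologic and relevant to stroke etiology". A separate sentence in that section says that etiology is assigned by TOAST and ESUS criteria.

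**Powered hypothesis.** Statistical analysis opens with "The sample size calculation is based on the aforementioned primary hypothesis (Table 2"), but the hypothesis it goes on to state is that the enhanced work-up "leads to a reduction in the number of strokes classified as cryptogenic from 30 to 25" %. All planning figures concern that classification: 30 % against 25 %, 13 % discordant pairs split 9 % and 4 %, 396 patients, 79 % power. It then says that the hypothesis will be tested by a two-sided McNemar test. An interim look at 264 patients stops the study if p is at most 0.004. Otherwise the primary endpoint is tested at 0.046.

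**The concern.** The cross-reference to Table 2 does not lead to the variable that was powered. Cryptogenic status is listed in Table 2 neither as a primary nor as a secondary outcome. A reader of Study outcomes would run McNemar's test on listed findings. A reader of Statistical analysis would run it on cryptogenic classification.

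Three things depend on which is meant: the variable behind the confirmatory p-value, the variable behind the interim stopping decision, and whether the 79 % describes the primary outcome at all. If the two variables gave different answers, this document would not say which one decides.

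**Working it through.** **Step 1. Are the two variables the same by definition?**

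| | Declared outcome | Powered variable |
|---|---|---|
| Where | Abstract; Study outcomes; Table 2; Discussion | Statistical analysis |
| Variable | Detection of a listed pathologic finding | Stroke classified as cryptogenic |
| Defined by | List in Stroke etiology | TOAST and ESUS criteria, cited there |
| Direction | Increase | Decrease |
| Planning figures | None | 30 %, 25 %, 9 %, 4 % |

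They would be exact complements only if a stroke were cryptogenic precisely when no listed finding is present. No sentence says so. They separate for any patient whose cause is classified on grounds outside the list. Such a patient is not cryptogenic yet has no listed finding, and a new listed finding raises the detection rate without lowering the cryptogenic count. The criteria themselves are cited, not reproduced, so the number of such patients cannot be derived here.

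If they were complements, the planning figures would imply that routine work-up finds a listed abnormality in 100 − 30 = 70 % of patients and enhanced work-up in 100 − 25 = 75 %. The article states neither rate.

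**Step 2. Reproduce the stated power.** Inputs from Statistical analysis: n = 396, net difference d = 0.09 − 0.04 = 0.05, total discordance s = 0.09 + 0.04 = 0.13, two-sided alpha 0.05 (z = 1.96).

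Power = Φ[(d√n − z√s) / √(s − d²)]

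= Φ[(0.05 × 19.90 − 1.96 × 0.3606) / √(0.13 − 0.0025)]

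= Φ[(0.995 − 0.707) / 0.357] = Φ(0.807) = 79.0 %.

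The same formula returns n = 396 for 79 % power. At the final level of 0.046 the power is 78.0 %. The calculation is sound for cryptogenic status.

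**Step 3. What follows for the declared outcome?** The formula needs d and s for listed findings, and the article gives neither. The rows below other than the protocol's own are assumptions, with n = 396 and two-sided alpha 0.05. The split is s/2 ± d/2.

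| Net gain | Discordance | Split | Power |
|---|---|---|---|
| 3 points | 13 % | 8 % / 5 % | 38 % |
| 5 points | 20 % | 12.5 % / 7.5 % | 61 % |
| 5 points | 13 % | 9 % / 4 % (protocol, cryptogenic) | 79 % |
| 5 points | 10 % | 7.5 % / 2.5 % | 89 % |
| 7 points | 15 % | 11 % / 4 % | about 95 % |
| 8 points | 13 % | 10.5 % / 2.5 % | 99 % |

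For the 7-point row: Φ[(0.07 × 19.90 − 1.96 × 0.3873) / √(0.15 − 0.0049)] = Φ[(1.393 − 0.759) / 0.381] = Φ(1.66), about 95 %.

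The 79 % carries over if listed findings happen to have the same gain and discordance. The article does not say that they do.

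**The case against.** The best defence is that cryptogenic status was meant as the per-patient form of the primary outcome. Statistical analysis presents its hypothesis as the one in Table 2 and later calls what is tested the primary endpoint. The listed findings are those relevant to etiology and stand under the heading Stroke etiology. The Discussion motivates the aim by strokes of unknown cause. This reading is possible, but no sentence states it, and the Stroke etiology section defines findings and etiology separately.

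The defence does limit what can be claimed. Three stronger readings are not supported:

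- *The p-value and the stopping decision are certainly computed on the wrong variable.* The McNemar sentence appears to refer to the cryptogenic hypothesis, but the interim sentence names no variable and the final test is attached to the primary endpoint. The text is ambiguous.
- *The study is underpowered for its declared outcome.* That follows only if the gain is held at 5 points and the discordance is raised. At 30 % discordance this gives 44 %, but with a 17.5 % / 12.5 % split, so the reverse discordance is 12.5 % against the protocol's 4 %. Keeping the 4 % and letting the forward part rise to 11 % gives about 95 %.
- *The classification system is left wholly open.* Stroke etiology names both TOAST and ESUS, but the section on the baseline visit records TOAST at discharge, before the additional ECG monitoring is evaluated.

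An unseen analysis plan may also settle the choice before the data are examined. That would not remove the contradiction between two sections of this article.

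**Conclusion.** The point holds as an inconsistency in the document. The sample size section cites the Table 2 hypothesis and then powers, and appears to test, a different variable that the article never equates with it. The 79 % is correct for cryptogenic status only.

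The power for the declared outcome is unstated, and the direction of any error is unknown. The examples from 38 % to 99 % show only how strongly power depends on the two missing inputs. They are not estimates for this trial, and they rest on 396 evaluable pairs and the normal approximation.

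The correction matters because the variable decides what the confirmatory test and the early stopping rule act on.

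**What to change.** Use one per-patient binary variable in Table 2, the McNemar test, the interim stopping rule and the power statement. Either of two repairs is consistent:

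- **(a) Listed findings primary.** Define the variable as at least one finding from the Stroke etiology list, enhanced against routine work-up, and use it throughout. Make cryptogenic status secondary. Label the 30 %, 25 %, 9 % and 4 % as borrowed from that classification, and show power over a range of both net gain and discordance.
- **(b) Cryptogenic status primary.** Name it as primary in Table 2 under one stated system (TOAST is already recorded at discharge). Keep the McNemar plan and the 79 %, and make the detection rate secondary.

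Both need only changes of wording and no new data. Under (a) the 79 % becomes a conditional figure. Under (b) it stands, but the outcome declared in the Abstract, Study outcomes and Discussion has to be reworded to match.

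### The interim look at 264 enrolled patients is labelled 67 %, but that is a fraction of the 396 patients with both work-ups; 264 enrolled is about 53 to 56 % of the planned information

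*Protocol article*

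**What the plan says.** All the relevant text is in the Statistical analysis section of the protocol article.

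- **Analysis target.** The calculation rests on "A sample size of 396 patients which receive both the enhanced as well as the routine diagnostic work-up", and this number "would provide a power of 79" per cent.
- **Planning assumptions.** The design is paired, "with assumed 13 % discordant pairs: 9 % diagnosed as cryptogenic stroke by routine work-up" only and "4 % diagnosed as cryptogenic stroke by enhanced work-up" only. The test is a two-sided McNemar test at 0.05.
- **Enrolment target.** After allowing for a drop-out of about 20 %, the section asks for 475 patients to be enrolled. The Study schedule section repeats 475 as the enrolment figure.
- **Interim.** One look at α1 = 0.004 "will be performed when 264 patients (67 %) are enrolled in the study". If the boundary is not reached, the final test uses α2 = 0.046.
- **Stopping rule.** "If p is ≤ α1 at the interim analysis, the study will be terminated".

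**The concern.** The section works with two counts: patients enrolled (target 475) and patients who have both work-ups and so contribute a pair to the McNemar test (target 396). The interim is triggered by the first count but labelled with a percentage of the second. No consistent reading gives 67 % for 264 enrolled patients.

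Two things are at stake. The first is that the instruction is ambiguous: trial staff cannot tell whether to run the look at 264 enrolled or at 264 pairs, and these points lie more than 50 enrolments apart. The second is that, if the sentence is followed as written, the look rests on fewer pairs than its label says and is less likely to be conclusive.

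Enrolment also comes before the data. According to the section on the study ECG and core lab, recording starts after enrolment, runs for up to 10 days and is then read externally. If the data were cut on the day the 264th patient enrolled, still fewer pairs would be complete.

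**Working it through.** **Inputs** (all from Statistical analysis): 396 pairs; 475 enrolled; drop-out about 20 %; 264 enrolled at the interim; discordant proportions 0.09 and 0.04; α1 = 0.004 and α2 = 0.046, two-sided.

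**Step 1: reproduce the stated power.** With total discordance p = 0.09 + 0.04 = 0.13 and difference d = 0.09 − 0.04 = 0.05, the normal approximation for McNemar's test is

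Power = Φ[(d√n − z√p) / √(p − d²)].

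For n = 396 and z = 1.960: (0.995 − 0.707) / 0.357 = 0.807, and Φ(0.807) = 0.790. The stated 79 % is reproduced, so 396 is the number of pairs analysed.

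**Step 2: reproduce the label.** 264/396 = 66.7 %. The 67 % arises only against the 396 pairs. Against enrolment, 264/475 = 55.6 %.

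**Step 3: convert 264 enrolled into pairs.** The article's step from 396 to 475 corresponds to 396 × 1.2 = 475.2. A true 20 % loss would need 396/0.8 = 495 enrolled, and 475 enrolled would then yield 475 × 0.8 = 380 pairs. Both conversions are shown because the article does not say which it means.

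| Conversion | Pairs at 264 enrolled | Fraction of planned pairs | Enrolled needed for 264 pairs |
|---|---|---|---|
| Article's ratio 396/475 | 264 × 396/475 = 220 | 220/396 = 55.6 % | 264 × 475/396 = 317 |
| True 20 % loss | 264 × 0.8 = 211 | 211/396 = 53.3 % (211/380 = 55.6 %) | 264/0.8 = 330 |

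**Step 4: chance of reaching α1 under the planned effect.** Same formula with z = 2.878 for two-sided 0.004. For n = 264: (0.812 − 1.038) / 0.357 = −0.631, and Φ = 0.264. The simulation column uses 400,000 multinomial runs with the asymptotic McNemar test.

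| Pairs at the look | Normal approximation | Simulation |
|---|---|---|
| 264 | 26.4 % | 25.4 % |
| 220 | 20.3 % | 19.2 % |
| 211 | 19.2 % | 18.0 % |

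With the exact version of the test the three values are 21.9, 15.6 and 14.4 %. The level is lower and the pattern is the same.

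**Step 5: overall type I error.** 0.004 + 0.046 = 0.05, so the split satisfies the Bonferroni bound whatever the timing. With a bivariate normal and correlation √t between the two looks, the overall two-sided level is 0.0467 at t = 66.7 %, 0.0472 at 55.6 % and 0.0473 at 53.3 %.

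**Step 6: overall power.** In the simulation with 396 pairs at the final analysis, two-stage power is 79.1 % whether the look is at 264, 220 or 211 pairs.

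**The case against.** The strongest reply is that this is a slip in one word. 264 is exactly two thirds of 396, so the design calculation very probably placed the look at 264 pairs. On that view the fraction is right and only the reference to enrolment is wrong. This is plausible and it decides which repair is the natural one. It does not remove the inconsistency, because the same section uses enrolment for the 475 as well.

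The second reply is that the primary test is hardly affected. Steps 5 and 6 confirm this. The final level does not need to be recomputed from the actual fraction, and the look is too early only in the sense of earlier than its label.

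The third concerns the 53 % end of the range. It combines a true 20 % loss with a target of 396 that 475 enrolled would then miss. On the article's own ratio the fraction is 55.6 %. This is fair, and it is why a range is given.

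The fourth is that incomplete ECG readings matter only if the data are cut on the day of the last enrolment. If the analysis waits for those patients' results, the point falls away. The article does not say which is meant.

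A reader might go further and infer that the mislabelled trigger damages the secondary outcomes: stopping at 264 enrolled would lose 211 of 475 patients (44 %) and widen secondary intervals by √(475/264) = 1.34, and would end the 12-month follow-up. The document does not support this.

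- The loss occurs only if the boundary is reached, roughly an 18 to 26 % event under the planned effect.
- It would largely remain with a corrected trigger: at 330 enrolled, 145 of 475 (31 %) would be lost and the factor would be √(475/330) = 1.20.
- Stopping once the primary question is answered is a design choice. The article powers the study on the primary hypothesis alone.
- One secondary outcome does concern "recurrent vascular events and clinical outcome after AIS at 3 or 12 months after the index stroke", but nothing in the article says that follow-up of patients already enrolled would cease. Study design and Study follow-up both provide for it at 3 and 12 months.

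What happens after a crossing could be clarified separately. It is not an effect of the label.

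**Conclusion.** The point holds as an error of denominator. As written, the interim takes place at about 53 to 56 % of the planned pairs and not at 67 %. Under the planned effect its chance of being conclusive falls from about 25 to 26 % to about 18 to 20 %, a loss of roughly a quarter of that chance. Overall type I error stays at or below 0.05 and overall power at about 79 %, so the validity of the primary result is not in question.

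This rests on the literal reading of the trigger, on the planned discordance of 9 % and 4 %, on losses falling evenly over recruitment, and, for overall power, on 396 pairs at the final analysis. If the trigger was meant as 264 pairs, the fraction stands and only the wording needs correcting. Either way the sentence cannot stay as it is.

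**What to change.** Reword the trigger so that count and percentage share a denominator. The preferable version is that the interim is performed when 264 patients (67 % of 396) have both work-ups completed and read, including the core-lab ECG result. That corresponds to about 317 enrolled on the article's inflation, or 330 at a true 20 % loss.

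The alternative is to keep 264 enrolled and restate the fraction as about 56 %, accepting the lower chance of a conclusive look.

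In both cases α1 = 0.004 and α2 = 0.046 can remain. The change should be made before the look is taken. It costs one sentence; under the first option the interim also falls some 53 to 66 enrolments later (317 − 264 and 330 − 264).

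### The 0.004/0.046 split keeps the overall level below 5 % but attains only about 4.7 %; deriving the final level from the joint distribution would recover about one point of power

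*Protocol article*

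**What the plan says.** All of this is in the protocol article, Methods, Statistical analysis.

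- Test: "The hypothesis will be tested using the McNemar-Test (two-sided, α = 0.05").
- Size and power: the calculation uses 396 patients, each having both work-ups. The section says that this number "would provide a power of 79 % to detect a difference in the number of strokes classified as cryptogenic".
- Assumed effect: the cryptogenic share falls "from 30 % after routine diagnostic work-up to 25 % after enhanced diagnostic work-up". The split of the discordant patients is given in two parts. The first part reads "with assumed 13 % discordant pairs: 9 % diagnosed as cryptogenic stroke by routine work-up" only. The part in the other direction reads "4 % diagnosed as cryptogenic stroke by enhanced work-up but not according to routine diagnostic work-up".
- Interim look: "An interim analysis (with a significance level of α1 = 0.004") after 264 patients, given as 67 %. The study ends if the interim p-value is at or below that level.
- Final look: two-tailed level 0.046, with the closing statement that "the overall significance level will be 5" %.

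The section names no boundary family or spending function. It does not say that the 5 % is spent in full, nor which alpha and which looks lie behind the 79 %.

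**The concern.** The levels 0.004 and 0.046 look like 5 % divided by subtraction. That is how one divides alpha between tests whose dependence is unknown. Here the dependence is known: the final analysis contains the interim patients, so the two statistics are strongly correlated and their rejection regions overlap. The probability of rejecting at either look is then less than the sum of the two levels.

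What is at stake is efficiency, not validity. Unspent alpha makes the final threshold stricter than it needs to be, in a study whose planned power is already just under 80 %. A reader may also take 5 % as the attained level, when it is only a bound.

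**Working it through.** **Inputs** (all from Statistical analysis): 396 pairs; interim at 264; α1 = 0.004; α2 = 0.046; discordant cells 9 % and 4 %, so the difference is d = 0.09 − 0.04 = 0.05 and the discordance is ψ = 0.09 + 0.04 = 0.13.

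**1. The plan's own level.** 0.004 + 0.046 = 0.050. The stated 5 % reproduces exactly as an additive split.

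**2. Attained level.** The critical values are 2.878 for 0.004 and 1.995 for 0.046. Under the null, the two standardised statistics are approximately bivariate normal with correlation √(264/396) = √0.667 = 0.816. The overall level is

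1 − P(|Z1| < 2.878, |Z2| < 1.995) = 0.0467.

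The unspent part is 0.0500 − 0.0467 = 0.0033. A simulation of the uncorrected McNemar test at both looks under the null (6.5 % in each discordant cell) gives 0.0459. This is slightly lower because the test is discrete.

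**3. Sensitivity to the information fraction.** The interim is triggered by patients enrolled, whereas 396 is the number before the drop-out allowance and 475 is the enrolment target. If the fraction is 264/475 = 0.556, the attained level is 0.0472.

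**4. Final level that would use 5 %, with α1 = 0.004.** Solve 1 − P(|Z1| < 2.878, |Z2| < c) = 0.05 for c and convert c to a two-sided level.

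| Information fraction | Level attained by 0.004/0.046 | α2 giving 5 % overall |
|---|---|---|
| 264/396 = 0.667 | 4.67 % | about 0.0494 |
| 264/475 = 0.556 | 4.72 % | about 0.0488 |

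**5. The stated power.** The usual McNemar formula is Φ((d√n − z√ψ)/√(ψ − d²)). With n = 396, d√n = 0.995, √ψ = 0.3606 and √(ψ − d²) = √0.1275 = 0.3571:

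- single look at 0.05: (0.995 − 1.960 × 0.3606)/0.3571 = 0.807, power 79.0 %
- single look at 0.046: (0.995 − 1.995 × 0.3606)/0.3571 = 0.772, power 78.0 %

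Other calculations for 396 pairs:

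| Calculation | Power |
|---|---|
| Two looks, 0.004/0.046, normal approximation | 77.9 to 78.6 % |
| Two looks, 0.004/0.046, simulation, uncorrected test | 79.0 % |
| Single look at 0.046, exact enumeration, uncorrected test | 79.0 % |
| Single look at 0.05, exact enumeration, uncorrected test | 80.1 % |

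The stated 79 % thus arises from one look at 0.05 by formula, and equally from the two-look design by simulation.

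**6. Gain from step 4.** Simulating the uncorrected test with 0.004/0.0494 at 396 pairs gives about 80.1 %, against 79.0 % with 0.046, a gain of about 1.1 points. Under the null the same pair simulates at 0.0499 to 0.0503 across separate runs.

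**The case against.** **The 5 % is correct as stated.** A significance level is the permitted maximum, and a procedure that attains 4.67 % is a valid 5 % procedure. This stands in full. A reader might infer from the 4.7 % figure that the stated type I error is wrong, but the documents do not support that: they never say the alpha is exhausted, and the deviation is on the safe side.

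**The additive split is robust.** It holds whatever the timing of the interim look and whatever the correlation. This also stands, and it is the real cost of the alternative. A level of 0.0494 fixed for 0.667 but applied at 0.556 would give about 5.05 % by the formula in step 2.

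**The power may already allow for the interim look.** A reader might infer that the 79 % was computed as a single test at 0.05, because that level is named next to it and the usual formula returns 79.0 %. The inference cannot be sustained. The text does not say so, the 0.05 can be read as the overall level that is then split, and the two-look design also simulates at 79.0 %. The differences between approximations are as large as the effect of the interim look.

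**The plan adopts no named boundary.** A reader might compare 0.046 with the final level of an O'Brien-Fleming-type design and conclude that the pair is mismatched. The section claims no such design, and a strict interim threshold is a legitimate choice.

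**The effect is small.** It is: about 0.3 points of alpha and one point of power, with assumed discordance rates that are themselves uncertain. What remains is that the loss is real, can be calculated, and is avoidable at little cost.

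**Conclusion.** The point holds as an efficiency and wording matter. The 0.004/0.046 split controls the overall level but ignores the correlation between looks. The attained level is about 4.7 % (4.67 % at 0.667, 4.72 % at 0.556), so 5 % is an upper bound and about 0.3 percentage points are unspent. Using them is worth about one point of power at 396 pairs (79.0 % to 80.1 %). There is no type I error inflation, and neither the 79 % power nor the sample size is shown to be wrong.

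This rests on the bivariate normal approximation for the two looks, an information fraction between 0.556 and 0.667, the assumed 9 % and 4 % discordant cells, and, for the simulated power, the uncorrected McNemar test. With the exact binomial or the continuity-corrected test, single-look power at 0.05 is lower (76.4 % and 76.0 %), so the version used matters more than this adjustment does. Low priority.

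**What to change.** Either of two changes, made before any interim data are seen:

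1. Keep α1 = 0.004 and state that α2 will be computed from the joint distribution of the two looks at the actual information fraction, to give 5 % overall (about 0.0494 at 0.667, about 0.0488 at 0.556). Name the McNemar version and confirm the attained level for it by enumeration or simulation, because the test is discrete.
2. Keep 0.004/0.046 and describe 5 % as an upper bound from an additive split.

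In both cases, add one clause giving the alpha and the looks on which the 79 % is based.

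The cost is one or two sentences and no extra patients. The first option has one downside: error control then depends on the realised information fraction, a condition that the additive split does not need.

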**Methods/Design:**

Prospective observational single-center study in 475 patients with acute ischemic stroke and without known atrial fibrillation. Patients will receive routine diagnostic care in hospital as wells as brain MRI, cardiac MRI, MR angiography of the brain-supplying arteries and Holter-monitoring for up to 10 days. Study patients will be followed up for cardiovascular outcomes at 3 and 12 months after enrolment.

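### The enrolment target of 475 adds 20 % to 396 instead of allowing for a 20 % loss; at that loss 380 pairs remain and power is about 77 %, not 79 %

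*Protocol article*

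**What the plan says.** The sample size paragraph of the Statistical analysis section refers to "A sample size of 396 patients which receive both the enhanced as well as the routine diagnostic work-up" and says that this number "would provide a power of 79" %. The test is fixed in the same paragraph: "The hypothesis will be tested using the McNemar-Test (two-sided, α = 0.05"). The planning effect is a fall in cryptogenic strokes "from 30 % after routine diagnostic work-up to 25 % after enhanced diagnostic work-up", "with assumed 13 % discordant pairs": "9 % diagnosed as cryptogenic stroke by routine work-up but not according to enhanced diagnostic work-up", and 4 % in the opposite direction.

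The paragraph closes with the enrolment figure: "Taking into account a drop-out rate of about 20 %, 475 patients will have to be enrolled in the study". The Abstract repeats the target ("Prospective observational single-center study in 475 patients with acute ischemic stroke"), and so does the Study schedule section. The article shows no inflation formula and gives no other drop-out rate.

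**The concern.** The 396 are patients who contribute a pair to the McNemar test, so 396 has to be what is left after losses. A drop-out rate is ordinarily a share of the patients enrolled, and allowing for it means dividing by one minus the rate. The printed target is instead what results from multiplying by one plus the rate, which always falls short.

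If enrolment and drop-out both turn out exactly as planned, the primary test has fewer pairs than its power statement assumes. There is no reserve to absorb this, since the plan's power at 396 is 79 % to begin with.

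**Working it through.** **Inputs**, all from the Statistical analysis section: 396 pairs; 9 % and 4 % discordant; McNemar test, two-sided alpha 0.05; final alpha 0.046 after an interim look at 264 patients with alpha 0.004; drop-out about 20 %; 475 enrolled.

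**Step 1: consistency of the effect assumptions.** 9 % + 4 % = 13 % discordant, and 9 % − 4 % = 5 points = 30 % − 25 %. These agree.

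**Step 2: reproduce the stated power.** With d = 0.05 and p = 0.13, the normal approximation is

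power = Φ[(d√n − z√p) / √(p − d²)],

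where √p = 0.3606 and √(p − d²) = √0.1275 = 0.3571.

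For n = 396 and z = 1.960: (0.9950 − 0.7067) / 0.3571 = 0.807, so power = 79.0 %. The plan's figure reproduces, so the inputs have been read as intended.

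**Step 3: check the enrolment target.**

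- Needed for 396 after a 20 % loss: 396 / (1 − 0.20) = 495, which is 20 more than stated.
- Adding 20 % to 396: 396 × 1.20 = 475.2, which matches the printed 475.
- Left from 475 after a 20 % loss: 475 × 0.80 = 380, which is 396 − 380 = 16 short.
- Largest loss at which 475 still leaves 396: 1 − 396/475 = 79/475 = 16.6 %.

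**Step 4: power at 380 pairs.** Same formula, alpha 0.05: (0.9747 − 0.7067) / 0.3571 = 0.751, so power = 77.4 % (77.35 % before rounding). The loss is about 1.7 points.

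**Step 5: like for like under other versions of the test.**

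| Calculation | 396 pairs | 380 pairs |
|---|---|---|
| Normal approximation, alpha 0.05 | 79.0 % | 77.4 % |
| Simpler normal approximation, alpha 0.05 | 78.8 % | 77.1 % |
| Uncorrected McNemar test, enumerated, alpha 0.05 | 80.1 % | 78.4 % |
| Exact binomial test, alpha 0.05 | 76.4 % | 74.5 % |
| Continuity-corrected test, alpha 0.05 | 76.0 % | 73.9 % |
| Normal approximation, final alpha 0.046 | 78.0 % | 76.3 % |
| Two looks, 0.004 and 0.046 | 78.1 % | 76.3 to 76.4 % |

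The range in the last cell reflects how many evaluable pairs the interim analysis holds. In every row the fall from 396 to 380 pairs is between 1.7 and about 2 points. The last two rows are lower at both sample sizes because of the smaller final alpha, not because of drop-out.

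**The case against.** **The rate is only approximate.** The text says about 20 %, and 475 is sufficient if the loss does not exceed 16.6 %. This stands to the extent that the shortfall is conditional on the loss. It does not rescue the figure: 16.6 % would normally be written as about 17 %, and the match with 396 × 1.20 points to multiplication. The approximation also runs the other way: at 22 % loss, 475 leaves about 370 pairs and about 76 % power.

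**Drop-out is not defined in the article.** Patients are followed by telephone at 3 and 12 months, and a loss there would not remove a pair from the primary test, because the work-ups are finished a few days after discharge. This is a fair reason to word the correction in terms of evaluable pairs. Even so, a sentence that moves from 396 patients with both work-ups to 475 enrolled is most naturally about losing such pairs.

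**The effect is small.** This stands. The uncorrected test, enumerated, still has 78.4 % power at 380 pairs. Uncertainty in the planning assumptions matters more: with the 5-point difference held, total discordance of 12 % or 14 % instead of 13 % moves the power at 380 pairs to 80.6 % or 74.2 %.

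**A stronger reading to avoid.** A reader might set 76 % at 380 pairs against the stated 79 % and ascribe the whole gap to the inflation error. About 1.1 points of that gap come from using alpha 0.046 instead of 0.05, and they are already present at the full 396 pairs (78.0 % against 79.0 %, before rounding 77.98 % against 79.03 %). That is a separate matter from drop-out.

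**Conclusion.** The enrolment target is wrong as written, and the error is minor. The figures 396, about 20 % and 475 cannot all hold if drop-out means the share of enrolled patients who do not yield a pair. At a 20 % loss the primary test has 380 pairs and about 77.4 % power at two-sided alpha 0.05 instead of 79 %; at the final alpha of 0.046 the corresponding fall is from 78.0 % to 76.3 %. The sizes rest on the plan's own discordance assumptions and on the normal approximation that reproduces its 79 %.

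A reader might infer that the study is seriously underpowered or that its conclusions are compromised. The documents do not support that. The type I error, the test and the outcome are untouched, and there is no shortfall at all if the loss of evaluable pairs stays at or below 16.6 %.

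**What to change.** Keep 475 and correct the closing sentence of the sample size paragraph in one of two ways:

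- state that a 20 % drop-out leaves 380 evaluable patients, with about 77 % power at two-sided alpha 0.05; or
- state that 475 enrolled supports 396 evaluable patients only if the loss of evaluable pairs is at most 16.6 %.

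In either case, note that 495 is the enrolment consistent with 396 pairs and a 20 % loss.

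Both wordings need no further patients and leave the 475 in the Abstract and Study schedule as it is. The price is that the stated power, or the tolerated drop-out, looks slightly less favourable. Raising the target to 495 would preserve 79 % at a 20 % loss, but it means 20 more patients having both work-ups and a change to every place that prints 475.
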